### 11.3.1 Description of Study Assessments

The following study assessments and procedures will be conducted as part of the clinical trial:

#### Demographics

The date of birth, gender and race of the infant will be recorded. Gestation, multiplicity, birth weight and resuscitation at delivery, including Apgar scores, will be documented.

Maternal age will be recorded. We will also record administration of antenatal steroids, preterm premature rupture of membranes (evidence of and duration of), intra-partum antibiotic use, the mode of delivery and indication for mode of delivery.

#### Physical Examination

The complete physical examination of the infant will include the evaluation of the cardiovascular, dermatological, musculoskeletal, respiratory, gastrointestinal, neurological systems. Weight and rectal temperature will be recorded.

#### Vital Signs

Vital signs will be recorded for all subjects and will include: blood pressure (BP), temperature (°C), pulse, and respiratory rate. Vital signs will be obtained at Baseline.

#### Concomitant Medications

Medications to be documented on the CRF include

- Postnatal corticosteroids for ventilator dependence
- Medical treatment for a patent ductus arteriosus
- Medical management of Necrotising enterocolitis ( $\geq$  Bell's stage 2)
- Intravitreal injection for retinopathy of prematurity

No medications are restricted in the treatment of the infants as a result of participating in this trial.

#### Chest Compressions

Chest compressions delivered in DR

#### Rectal Temperature

Rectal temperature on admission to NICU. Recording rectal temperature in newborns provides the most accurate temperature recording in comparison with other methods and is performed routinely in NICUs.

#### Adrenaline Administration

Adrenaline administration by intravenous or endotracheal route in DR

#### Intubation for Respiratory Failure

Respiratory failure in the NICU defined as  $\geq 2$  of:

Clinical signs – worsening tachypnoea; grunting; subcostal, intercostal and/or sternal recession

Acidosis – pH  $< 7.2$  on 2 blood gases (arterial or capillary)  $\geq 30$  minutes apart

$O_2 - FiO_2 > 0.4$  to keep  $S_pO_2 \geq 90\%$  for  $> 30$  minutes

$PCO_2 > 9.0$  kPa on 2 blood gases (arterial or capillary)  $\geq 30$  minutes apart

Apnoea – recurrent apnoea treated with mask ventilation

Assessment of Bronchopulmonary Dysplasia as a supplemental  $O_2$  therapy at 28 days of life

#### Assessment of Chronic Lung Disease Prematurity

Need for supplemental O2 at 36 weeks corrected gestational age (CGA) determined by physiological oxygen reduction test

#### 11.3.2 Endpoints assessments

##### Eff cacyAssessment

The primary outcome – whether the infant has been intubated for respiratory failure – will be determined at 120 hours of life.

The following secondary outcomes will be determined at the times indicated:

- Intubation in the delivery room (DR)
- Number of attempts taken to successfully intubate in the DR
- Chest compressions in the DR
- Adrenaline administration in the DR
- Rectal temperature on admission to the NICU
- Bronchopulmonary dysplasia (BPD) – supplemental O2 at 28 days of life
- Chronic lung disease of prematurity (CLD) – need for supplemental O2 at 36 weeks corrected gestational age (CGA) determined by physiological oxygen reduction test
- Death before hospital discharge

The following secondary outcomes will be measured during the infant's hospitalisation and determined at discharge:

- NICU intubation
- Surfactant use
  - Number of doses, including total dose
  - Intra-tracheal surfactant received post-intervention
  - Doses of post-intervention surfactant
- Incidence of pneumothorax
- Incidence of pulmonary haemorrhage
- Mechanical ventilation
- Days of mechanical ventilation
- Use of postnatal corticosteroids for ventilator dependence
- Days of duration of respiratory support (endotracheal ventilation, high-frequency oscillatory ventilation, CPAP, heated humidified high-flow nasal cannula O2, low flow nasal cannula O2)
- Medical treatment for a patent ductus arteriosus
- Surgical treatment for a patent ductus arteriosus
- Proven necrotising enterocolitis (≥ Bell's stage 2)
- Incidence of Intraventricular haemorrhage (IVH) (any and severe: IVH grade ≥ 3)
- Incidence of cystic periventricular leukomalacia
- Retinopathy of prematurity treated with laser photocoagulation or intravitreal injections
- Survival without BPD at hospital discharge
- Survival without CLD at hospital discharge
- Duration of hospitalisation
- Use of home oxygen therapy

##### Safety Assessment

The following safety evaluations will be performed during the study: adverse event monitoring. Surfactant has an excellent safety profile for use. Previously reported adverse effects include bradycardia and desaturation.

We will also record the number of intubation attempts in DR post oropharyngeal surfactant use.

#### 11.3.3 Screening procedure

Names of potential participants' parents(s)/guardians(s) will be obtained from the obstetric team, antenatal wards and clinics. They will be approached by a member of the research team or other senior doctor (neonatal consultant or registrar) to inform them of the study. We intend to recruit where possible, however it is likely the majority will be recruited when in-patients in the hospital e.g. antenatal wards or delivery ward. An information sheet will be provided to the parents to keep and the details of the study will be explained to them. They will then be invited to participate in the study.

Once informed consent is obtained, should preterm delivery prior to 29 weeks gestation ensue, then randomisation will occur at the time of delivery. There is no maximum duration between screening and randomisation, as long as delivery is prior to 29 weeks gestation. Informed consent is the only procedure that must be completed before the study begins.

During the screening period subjects will be evaluated for eligibility. Assessment of inclusion/exclusion criteria will be again assessed at the time of randomisation for the subject to continue in the study.

Informed consent will be obtained prior to enrolment in the trial.

#### 11.3.4 Baseline assessments

The following pre-treatment Baseline assessments/procedures will be performed prior to randomisation:

- confirmation of eligibility (review inclusion/exclusion criteria)
- informed consent

Following randomisation and obtaining consent, the following assessments/procedures will be done at baseline, (the day of birth):

- dispensing of study medication
- collection of vital signs, concomitant medications and demographics information
- physical examination
- rectal temperature
- chest compressions
- administration of adrenaline
- adverse events assessment

The recording of the incidence of chest compressions and adrenaline administration is the aim as these are not necessarily routine procedures.

#### 11.3.5 Subsequent study visits and procedures

The intervention in this study is a once-off administration of surfactant at birth. After this intervention, all other cares will be the same between infants in both arms.

Assessment of the incidence of intubation for respiratory failure is the goal and will be conducted at 120 hours post birth (visit 3).

Assessment of bronchopulmonary dysplasia will be at day 28 of life and assessment of chronic lung disease prematurity will be at CGA 36 weeks.

During hospitalisation, at all visits after and including baseline visit, the following assessments/procedures will occur:

- assess efficacy outcome measures
- assess safety (adverse event monitoring)
- dispense study medications
- record concomitant medications
- assess compliance with study medications

#### 11.3.6 Method of assigning Subjects to treatment groups

Infants will be randomised to receive oropharyngeal surfactant or CPAP (which is the standard of care) in a 1:1 ratio using variable block randomisation, with block sizes of 4, 6 and 8. Randomisation will be stratified by participating centre. The more prematurely an infant is born, the higher their risk is of being

intubated for respiratory support in the first 120 hours of life (primary outcome). It is important to ensure balance in the risk of reaching the primary outcome between the two treatment arms at study entry; thus we will also stratify the randomisation by gestational age (<26 weeks and 26-28 weeks inclusive).

Infants of multiple gestations will be randomised as individuals.

A computer-generated randomisation schedule will be prepared by an independent statistician who will not be involved with subsequent data analysis or interpretation. The schedule will be stored securely on a password protected computer. The randomization list will be numbered using sequential 6-digit randomization codes (e.g. NMH001, NMH001,...). Each group assignment – “OROPHARYNGEAL SURFACTANT” or “CONTROL” – will be written on a card that will be labelled with its corresponding 6-digit randomisation code (e.g. NMH001). Each card will be folded in half and placed in an opaque sealed envelope that will be labelled with the same 6-digit randomisation code. The envelopes will then be placed in sequential order (e.g. NMH001, NMH002, NMH003...) in separate boxes for the two gestational age strata for each centre. At each centre, the boxes containing the envelopes will be stored securely in the neonatal intensive care unit (NICU), as the clinical team will need to have access to the randomisation envelopes. An envelope from the appropriate box (<26 weeks or 26–28 weeks) will be opened immediately before birth.

#### Blinding

This is an open-label study. The study will not be blinded to investigator, subjects, or medical or nursing staff. We are not using a placebo, and in the event of the baby being randomised to the ‘CONTROL’ arm, then they will be commenced on CPAP immediately after birth.

The trial statistician will be blinded for data analysis, and will be kept unaware of treatment group assignments. The randomization schedule will be drawn up by an independent statistician, to facilitate this.

#### **11.4 Definition of end-of-trial**

The end of the trial will be when all infants have been recruited and the last baby has been discharged from hospital, in order to ensure all secondary outcomes have been recorded. On occasion, surviving premature infants have a surgical intervention (e.g. tracheostomy, bowel resection) that renders them dependent on technology (e.g. positive pressure respiratory support, parenteral nutrition). These infants may remain as hospital in-patients for months or years beyond their expected date of delivery (EDD). It is not possible to identify these infants at enrolment. If one such infant is enrolled in the study, waiting to collect their discharge-based secondary outcome data (date of discharge, duration of hospitalisation, receipt of home oxygen) would indefinitely defer the analysis of the primary outcome and other secondary outcome data for all participants. After enrolment is complete, it will be determined whether any infant who remains in hospital one month beyond their EDD remains in receipt of supplemental oxygen and their primary and other secondary outcome data (up to Section I of the Case Record Form) will be locked for analysis at that point. These infants will be followed to ascertain their date of discharge and duration of hospitalisation (Section J). The participation of infants who remain as in-patients 6 months after their EDD will be censored, and their duration of hospitalisation will be recorded at that point.

The Sponsors and/or the trial steering committee, however, have the right at any time to terminate the study for clinical or administrative reasons.

The end of the study will be reported to the REC and Regulatory Authority within 90 days, or 15 days if the study is terminated prematurely. The investigators will inform subjects and ensure that the appropriate follow-up is arranged for all involved.

A summary report of the study will be provided to the REC and Regulatory Authority within 1 year of the end of the study and within 6 months for paediatric studies. This is a legal requirement.

The end-of-trial is the date of the last visit/telephone follow-up/home visit of the last subject. The end of study visit forms should include:

- assessment of endpoints/outcome measures

- assessments of safety including adverse event collection
- assessment of compliance with study treatment(s)
- recording of concomitant medications

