#### Secondary endpoints analysis

Mortality is an intercurrent event that could potentially occur before observation of many of the secondary endpoints in this trial in addition to the primary endpoint. Most secondary outcomes will involve evaluation of the intervention effect to be expected in infants while alive. Analysis of secondary endpoints will be performed on the intention-to-treat set of all randomised infants. The exceptions to this are

- Number of attempts taken to successfully intubate in the delivery room – will only be assessed for those who need to be intubated in the delivery room (intubation in the delivery room is indicated by variable **dr\_infant\_intub.factor**)
- Rectal temperature on admission to NICU as well as NICU intubation will only be evaluated for infants who are admitted to NICU alive (identified by derived variable **nicu\_admission**)

|         |                                           |              |               |
|---------|-------------------------------------------|--------------|---------------|
| UCD CRC | SAP for the POPART trial                  |              |               |
| UCD CRC | Template: Statistical Analysis Plan (SAP) | Version: 1.0 |               |
|         |                                           |              | Page 13 of 19 |

- Bronchopulmonary dysplasia (BPD) – supplemental O2 at 28 days of life - will only be evaluated for infants who are alive at 28 days of life (infants alive at 28 days to be determined by the variable **bpd\_d28.factor** )
- Chronic lung disease of prematurity (CLD), the need for supplemental O2 at 36 weeks corrected gestational age (CGA) determined by physiological oxygen reduction test - will only be evaluated for infants who are alive at 36 weeks CGA (determined by the variable **cld\_36wks.factor** )
- Duration of hospitalisation will be summarized and analyzed both for infants who survive to hospital discharge and for the whole sample. A similar approach will be used for days of mechanical ventilation and days of respiratory support.

Each categorical secondary endpoint will be analysed using the same approach as the main analysis of the primary endpoint.

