For the time-to-event endpoint death before hospital discharge, Kaplan-Meier curves will be constructed to visualize the pattern of mortality over the study period, with median survival time reported with 95% confidence intervals. Cox proportional hazards regression will be used to quantify the hazard ratio for those treated with oropharyngeal surfactant vs standard-of-care. A Cox proportional hazards regression model will also be fitted to determine sensitivity of the estimated intervention effect to potentially relevant covariates; including centre, gestational age, birth weight, gender, mode of delivery (vaginal versus caesarean birth) and antenatal corticosteroid treatment.

Each numeric secondary endpoint (e.g. duration of mechanical ventilation, duration of hospitalisation), will be analysed using the following approach.

- Descriptive statistics will be calculated to compare the endpoint across treatment groups. This will include the frequency of missing data per treatment arm, minimum and maximum values, mean and standard deviation for symmetrically distributed variables and median and interquartile range for asymmetrically distributed variables. The difference in means (or medians where relevant) between treatment groups will be presented with a 95% confidence interval. Confidence intervals for the difference in means will use a Normal approximation while confidence intervals for the difference in medians will be calculated by bootstrap resampling.
- A superiority hypothesis test (two-sided independent sample t-test) will be carried out to test for a difference in means between control and intervention. Alternatively, if t-test assumptions are not valid, a Mann-Whitney U test will be carried out to test for a difference in the the endpoint between control and intervention.

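### SAP 5.1.1 treats hospital stays censored at 6 months past the due date as completed stays and, read literally, leaves those infants out of the survivor analysis

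*Combined protocol and SAP*

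**What the plan says.** Protocol 11.4 (Definition of end-of-trial) notes that a few surviving infants become technology-dependent and may stay in hospital for months or years past the expected date of delivery (EDD). Under its rule, those "who remain as in-patients 6 months after their EDD will be censored, and their duration of hospitalisation will be recorded at that point". By the protocol's own account, then, the stored value is a lower bound on the stay.

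SAP 5.1.1 (Secondary endpoints analysis) handles the endpoint as a number: "Each numeric secondary endpoint (e.g. duration of mechanical ventilation, duration of hospitalisation), will be analysed using the following approach". The comparison is a difference in means or medians with a 95% confidence interval. The test is stated as follows: "A superiority hypothesis test (two-sided independent sample t-test) will be carried out to test for a difference in means between control and intervention". There is a fallback: "if t-test assumptions are not valid, a Mann-Whitney U test will be carried out". Protocol 14.5.2 plans the same.

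On analysis sets, the SAP says: "Duration of hospitalisation will be summarized and analyzed both for infants who survive to hospital discharge and for the whole sample".

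Kaplan-Meier and Cox methods are specified only for death before discharge. SAP 5.3 (Missing data) is silent on censored stays, and SAP 6 declares no departure from the protocol.

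**The concern.** The protocol calls these stays censored, but the SAP supplies no method that uses the censoring. In the whole-sample analysis the recorded day enters as if the infant had gone home that day. In the survivor analysis, an infant who has neither died nor been discharged does not fit the stated definition. The longest stays would then leave that analysis through a criterion determined after randomisation.

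At stake is what the reported difference in days means. If the arms differ in the number of technology-dependent survivors, the whole-sample mean difference counts only part of their stay, and the survivor analysis may count none of it. Because no rule places these infants, the choice would fall to whoever codes the set.

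**Working it through.** **The plan's own figures.** The documents give no expected stay, no standard deviation and no count of long-stay infants, so this endpoint has no figure to reproduce. The arm size used below comes from Protocol 14.2 (46% v 28%, two-sided 5%, 80% power): n = [1.960·√(2·0.37·0.63) + 0.842·√(0.46·0.54 + 0.28·0.72)]² / 0.18² = 111.8. That is 112 per arm or 224 in total, as stated.

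**Where the cut falls.** With EDD at 40 weeks, the day of life at the cut is (40 − GA)·7 + 182.6:
- 23 weeks: 119 + 182.6, about day 302
- 28+6 weeks: 78 + 182.6, about day 261

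No stay can enter the analysis as longer than this.

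**Illustration (all inputs assumed).**
- 112 survivors per arm, GA uniform over 23 to 29 weeks
- ordinary discharge on average 10 days before EDD, SD 22 days
- cut at EDD + 183 days
- long-stay infants remain a further 180 days on average (exponential)

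A long-stay infant therefore exceeds an ordinary one by 183 + 10 = 193 days if cut, and by 193 + 180 = 373 days in truth. The expected mean difference is (excess number in one arm / 112) × that figure, and 0 if these infants are dropped.

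| Long-stay infants | True | Cut | Dropped |
|---|---|---|---|
| 3 v 0 | 3/112 × 373 = 10.0 d | 3/112 × 193 = 5.2 d | 0 |
| 1 v 0 | 3.3 d | 1.7 d | 0 |
| 3 v 3 | 0 | 0 | 0 |

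If the mean further stay is varied from 90 to 365 days (3 v 0), the true figure runs from 3/112 × 283 = 7.6 to 3/112 × 558 = 14.9 days. The cut figure stays at 5.2.

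**Standard errors, 3 v 0.** The variance of ordinary stays is 22² + 42²/12 = 484 + 147 = 631.
- Dropped: √(631/109 + 631/112) = 3.4 days.
- Cut: the affected arm's variance is 631 + (3/112)(109/112)·193² = 1,602, so the SE is √(1,602/112 + 631/112) = 4.5 days.
- True: the affected arm's variance is 631 + (3/112)(109/112)·373² + (3/112)·180² = 5,126, so the SE is about 7.2 days. The average SE in simulation is 7.0.

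**Effect on the tests.** In 2,000 simulated trials on these inputs (3 v 0), the t-test rejects in about 14% of trials with true stays and about 15% with cut stays. The Mann-Whitney test rejects in about 6% either way, and the median difference is about 1 day either way.

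A second simulation used 125 per arm and stays running 180 to 730 days past the cut. With 3 v 0 the mean difference was about 9 to 22 days true, 4 cut and 0 dropped. Medians and the Mann-Whitney statistic were identical to three decimals between true and cut stays. Dropping the infants did move them a little: with 5 v 0, the median difference went from about −1.3 to −0.1 days and the Mann-Whitney probability from 0.48 to 0.50.

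**The case against.** Four arguments limit the point.

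1. **The rank and median route is already in the SAP.** Long stays produce strong skew, and the SAP offers medians, bootstrap intervals and Mann-Whitney when t-test assumptions fail. On that route the cut does no harm. This stands, but the SAP sets no criterion for the switch, and the route helps only if the infants are kept.

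2. **The recorded mean has a coherent meaning.** Every infant is followed to discharge, death or the same horizon of EDD + 6 months. The whole-sample mean is then a restricted mean, and it is biased only if the target is unlimited stay. This stands, but neither document labels it so.

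3. **Exclusion from the survivor set is an inference.** The SAP names no variable for that set. The only listed status variable is death before discharge, and Protocol 11.4 describes these infants as surviving. If the set is coded as not dead, they stay in with their cut value. This stands: the text permits both codings.

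4. **Numbers and arm balance are unknown.** The protocol says only that such stays happen on occasion. With balanced numbers the mean difference does not shift on average.

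A reader might also infer that the cut turns a significant result into a non-significant one, by setting 10 and 5 days against a single standard error of about 3 days. That does not follow. The long stays that enlarge the difference also enlarge its standard error, and the rejection rates are nearly equal.

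**Conclusion.** There is a real gap between Protocol 11.4 and SAP 5.1.1. The protocol censors these stays; the SAP analyses them as complete and does not say where living, undischarged infants belong in the survivor set. The censored value arises for one secondary endpoint, probably in few infants. The primary endpoint is untouched.

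A mean difference describes stay only up to EDD + 6 months. On the assumed inputs with 3 v 0 such infants, it is about 10 days true, 5 cut and 0 if dropped (SEs about 7, 4.5 and 3.4 days). Those sizes rest wholly on assumptions about stay length and arm split. Median and rank results are unaffected by the cut provided the infants are kept.

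Two stronger readings are not supported. One is that the longest stays disappear from the comparison altogether: they remain in the whole-sample analysis, and their loss from the survivor analysis depends on how that set is coded. The other is that the surfactant arm, or any particular arm, would be flattered: the documents give no basis for a direction.

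**What to change.** In SAP 5.1.1:

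- State that infants alive and undischarged at EDD + 6 months are kept in both analysis sets.
- Choose the main comparison in advance. One option is the rank test with these stays ranked longest, reporting medians. The other is time from birth to discharge home alive, with these infants censored at the recorded day and death as a competing event, reporting cumulative incidence and median time. The second matches the protocol's word and also avoids counting early deaths as short stays.
- Label any difference in means as stay restricted to EDD + 6 months.

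This needs some SAP wording and a few lines of code. No new data are required, and the SAP already plans a competing-risks model for the primary endpoint. The downside is that an unrestricted difference in mean days is no longer the effect measure for this endpoint.
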